### Data collection

We will use the most recent 10-year period of police-reported traffic collision data. This project will be conducted municipality-wide, not focussed specifically on school zones as in Project 2A. Police reports of pedestrian-MVCs and bicycle-MVCs include the geographical coordinates of the collision, which will be mapped for the four municipalities. Collisions will be assigned to a feature either within a 30 m buffer-zone for point features (e.g. traffic lights) [32, 52–54] or within a 25 m buffer zone if along a roadway segment (e.g. traffic calming) [55–57]. As in other projects, potential built environment predictors will be extracted from the spatial database as described in Objective 1. The potential traffic features include (but are not limited to): 1) Traffic calming (including speed humps, chicanes, pinch points, etc.); 2) Changes in speed limits; 3) Curb extensions; 4) Traffic lights; 5) Stop signs; 6) One-way streets; 7) Level 2, uncontrolled pedestrian crossovers in residential areas; 8) Crossing guards; 9) Dead end roads; 10) Cycle lanes and cycle tracks. Location and installation dates for these built environment features will be obtained from municipality transportation departments where possible.

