### Data analysis

The analysis will start with descriptive statistics of each feature and pedestrian injury rates in each municipality (Vancouver, Calgary, Toronto, Montreal). We will model collision frequency pre/post installation of each built environment feature, in each municipality, stratified on active transportation mode (pedestrian/bicyclist). The outcome will be the collision rate per feature/month (time as the offset variable). A repeated measures Poisson regression (where the feature’s site acts as its own control) will be used to model rates of pedestrian-MVCs and bicyclist-MVCs pre and post installation of the feature, controlling for feature covariates. The pre-installation period without the feature will be designated as the reference value. For features that are implemented/installed along a length of roadway (e.g., speed limits, traffic calming) we will measure collision rates using incidence density/roadway meter/month. This rate will reflect the number of collisions per meter of roadway that had the feature. For those variables that are implemented/installed at a specific point (e.g. crossing guards, crosswalks) collision rates will be measured using incidence density/traffic feature/month.

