### Inter-municipality comparisons

After examining the effects of each feature within each municipality, we will conduct a similar analysis across all cities, using a categorical variable representing each municipality as one of the covariates. This will allow us to estimate the effect of the feature in different settings, and to assess which features are most effective in which context.

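### Project 2C gives crossing guards the same all-purpose monthly collision rate as permanent features, with no limit to the times a guard is present, which pulls the guard rate ratio toward 1

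*Protocol article*

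**What the plan says.** Crossing guards are item 8 of the ten potential features in Project 2C, Data collection. The article treats them as school guards: they appear under school context in the Objective 1 predictor list, and as school crossing guards in the Anticipated concerns of Project 2C.

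The collisions come from police files: "We will use the most recent 10-year period of police-reported traffic collision data". They are assigned to a point feature by distance alone, within 30 m. On scope, the section adds: "This project will be conducted municipality-wide, not focussed specifically on school zones as in Project 2A".

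The Data analysis section defines the outcome: "The outcome will be the collision rate per feature/month (time as the offset variable". The model is a repeated measures Poisson regression with the pre-installation period as reference. The rate is then adapted to the type of feature: per metre of roadway per month for linear features and, for point features, "For those variables that are implemented/installed at a specific point (e.g. crossing guards, crosswalks) collision rates will be measured using incidence density/traffic feature/month".

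Under Inter-municipality comparisons, the pooled analysis is meant "to assess which features are most effective in which context".

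No part of Project 2C restricts the collisions or the time offset to guard hours, school days or school months. No part states outright that all hours and months are counted.

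**The concern.** A crosswalk or a traffic light is there at all hours once installed. A school crossing guard is there around school travel on school days. If both are given collisions per feature-month with no further limit, the post-installation period for a guard includes nights, weekends and holidays when no guard is present. A guard who acts only while present cannot change those collisions, yet they enter both the pre and the post rate and push the ratio toward 1.

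Permanent features are not diluted in this way. An effective guard programme could therefore show a ratio near 1, and guards would look weaker than permanent features in the assessment of which features work best. Project 3B carries Objective 2 results into the municipal toolkit, so the reading would reach decision makers.

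**Working it through.** Project 2C states no sample size, event count or effect size, so there is no figure of the plan to reproduce. The check covers what the stated rate would estimate.

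**Inputs**
- Outcome: collisions per feature per month, time as offset (Project 2C, Data analysis).
- Assignment: distance only, 30 m for point features (Project 2C, Data collection).
- f, the share of pre-installation collisions in guard hours: not in the article; assumed from 0.1 to 0.7.
- RR, the true rate ratio in guard hours: not in the article; assumed 0.70 and 0.50.
- No effect outside guard hours: assumed.

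**Ratio scale.** Let L be the pre-installation rate per feature-month. Of this, fL falls in guard hours and (1 - f)L outside. After installation the rate is fL·RR + (1 - f)L. Dividing by L:

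observed ratio = f·RR + (1 - f) = 1 - f(1 - RR)

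| f | RR = 0.70 | RR = 0.50 |
|---|---|---|
| 0.1 | 0.97 | 0.95 |
| 0.2 | 0.94 | 0.90 |
| 0.3 | 0.91 | 0.85 |
| 0.5 | 0.85 | 0.75 |
| 0.7 | 0.79 | 0.65 |

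Example: f = 0.3, RR = 0.70 gives 1 - 0.3 × 0.30 = 0.91. With collisions and time limited to guard hours, the ratio stays at RR.

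**Absolute scale.** The expected change per feature-month is L - [fL·RR + (1 - f)L] = fL(1 - RR). Counting guard hours only gives fL - fL·RR, the same quantity. The absolute change is therefore not diluted; the out-of-hours collisions only add noise.

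**Events needed.** For 80% power at two-sided 0.05 with equal pre and post time, the Schoenfeld formula serves as an approximation to the two-period Poisson comparison: events = 4(1.960 + 0.842)² / (ln ratio)². At RR = 0.70 in guard hours only, this gives 247 events. To collect those, one needs 247 × (1 + observed ratio) / (f × 1.70) collisions at all hours.

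| f | Events needed, unrestricted | All-hours collisions that contain 247 in guard hours | Ratio |
|---|---|---|---|
| 0.2 | 8,201 | 1,409 | 5.8 |
| 0.3 | 3,530 | 925 | 3.8 |
| 0.5 | 1,189 | 538 | 2.2 |
| 0.7 | 566 | 372 | 1.5 |

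Under these assumptions, restricting the window loses events but gains power for the ratio.

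**Share of time is not share of collisions.** At an assumed 1 hour on 180 days up to 4 hours on 200 days, a guard is present for 180/8,760 = 2.1% to 800/8,760 = 9.1% of all hours. Child collisions may concentrate around school travel, so f may be far larger than this and cannot be read off it.

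**The case against.** The strongest reply is that the article gives only a rate unit. A per-month denominator is compatible with a numerator limited to school hours, and a journal article may leave such filters to the full protocol. Project 2C also cites earlier published crossing-guard work as the same approach, and that work may have used a time window. Part of this stands: that every collision in every month is counted is the natural reading, not an explicit statement. It does not remove the point. The article does not defer this outcome. It fixes the buffer, the offset, the reference period and the rate by feature type, and uses guards to illustrate the point type. The earlier work is mentioned without any time window.

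A second reply is that all-hours collisions per feature-month measure the net effect of placing a guard at a site, a legitimate quantity for a municipality. This stands, and is a reason to keep it as a secondary outcome. As a ratio, however, it cannot separate a weak guard effect from a strong one confined to few collisions. A difference in f between cities would also look like a difference in effect: at RR = 0.70, f = 0.3 gives 0.91 and f = 0.5 gives 0.85.

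Two stronger readings are tempting and not supported. A reader might infer that most of the measured rate comes from hours without a guard. That needs f below 0.5, which the article neither supports nor refutes. A reader might also extend the point to speed limits in force only at school times. The list includes changes in speed limits but mentions no time limit, so guards are the only clearly part-time item.

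Finally, guards are only a potential feature, included if enough installation dates can be obtained, and no formal ranking of features is specified. Both limit the reach of the point.

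**Conclusion.** The point holds for crossing guards. Following the stated rule, the pre/post rate ratio moves toward 1 for any f below 1. The size depends wholly on f, which the article does not give: at a true ratio of 0.70, the observed ratio runs from 0.94 (f = 0.2) to 0.79 (f = 0.7), so some bias remains even if most collisions fall in guard hours. This rests on three assumptions: the rate is applied as written, guards have no effect outside their hours, and the effect is reported as a ratio, as the Poisson model implies. The consequence is an unequal comparison of guards with permanent features, confined to one listed feature.

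**What to change.** In Project 2C, Data analysis, state that for crossing guards, and for any other included feature that operates only part of the time, the primary rate ratio uses collisions and time at risk within operating hours on school days. Apply the same window to the pre-installation period at the same site. If a city's file lacks clock time, restrict at least to school days in school months; this reduces the dilution without removing it. Keep all-hours collisions as a secondary outcome. Use out-of-hours collisions at the same sites as a negative control: a pre/post change there would point to a background trend or to an effect beyond guard hours.

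The cost is a few lines of text and a filter on police records already planned for use. It relies on those files carrying date and, preferably, time, and on knowing guard schedules. Fewer events remain for this feature, so in cities with few guard sites the restricted estimate may be imprecise.

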### Spatial analysis

This description and inference involves spatial point pattern analyses. There are two levels of analysis to consider: 1) The broad pattern of events across each study area–a consideration of first order effects (variation in the mean of a spatial process); and 2) The extent to which the events cluster or interact with one another, and around specific objects located in the built environment (second order effects). In this study, analysis of second order effects will focus on the clustering of events around each site pre and post installation. For example, a speed hump may displace vehicle flow to neighbouring streets and conversely a bicycle lane may draw bicycle flow from neighbouring streets. In either case, an area analysis is required to fully understand safety consequences both at and around the feature.

### Inter-municipality comparisons

After examining the effects of each feature within each municipality, we will conduct a similar analysis across all cities, using a categorical variable representing each municipality as one of the covariates. This will allow us to estimate the effect of the feature in different settings, and to assess which features are most effective in which context.

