### Data analysis

The primary outcome variable is the observed proportion of students arriving at school via active transportation. Direct observations of active transportation to school will be used to generate a numerator (students observed walking, bicycling, and other active transportation). The denominator is total observed non-school bus student arrivals (walking, bicycling, arriving by vehicle, and other). Children arriving by school bus will be excluded as they typically live further than walking distance. With the school as the unit of analysis, active transportation proportions will be modeled with built environment predictors using multivariable regression [41]. Sensitivity analysis will use different street network buffer distances. Categorical variables will be included in the model representing each of the sites (municipalities) to enable inter-jurisdictional comparisons. Separate models will also be estimated for each municipality.

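### Project 2C's cross-city model enters municipality only as a covariate, so it gives one common pre/post rate ratio per feature and cannot itself show how effects differ by city, as the text says it will

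*Protocol article*

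**What the plan says.** The Data analysis section of Project 2C sets out the core model: "We will model collision frequency pre/post installation of each built environment feature, in each municipality, stratified on active transportation mode (pedestrian/bicyclist"). The method is "A repeated measures Poisson regression (where the feature’s site acts as its own control"), and "The pre-installation period without the feature will be designated as the reference value". The effect of a feature is thus the post-installation rate divided by the pre-installation rate, estimated city by city and by travel mode.

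The section on Inter-municipality comparisons follows. Once the within-city effects have been examined, a similar analysis is run on the pooled data, "using a categorical variable representing each municipality as one of the covariates. This will allow us to estimate the effect of the feature". The sentence goes on to promise that effect for the various settings, and gives as a further purpose "to assess which features are most effective in which context".

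The Data analysis section of Project 2A is worded differently. It enters municipality as a covariate and, in addition, says that confounding and effect modification of the other predictors by municipality will be evaluated. Project 2C contains no counterpart to that second step.

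**The concern.** The text attaches to the cross-city model a result that the model, as described, does not produce. A municipality covariate lets the collision rate differ between cities. It does not let the change in that rate after installation differ between cities, and that change is the effect of interest.

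At stake is the between-city comparison. The protocol wants "to assess which features are most effective in which context", and Project 3B says that results from Objectives 1 and 2 will go into municipality-level reports used with the toolkit. The separate city models will give an estimate for each city, but setting four estimates side by side does not test whether they differ. The 2C section on anticipated concerns says that sample size and time before and after installation will vary by feature and municipality. One city's interval may therefore exclude 1 and another's include it because of precision alone.

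**Working it through.** Project 2C states no sample size, power or target effect, so there is no figure of the plan's to reproduce. The check concerns model structure.

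**Inputs from the protocol.** Poisson regression with time as offset; pre-installation as reference; site as its own control; four municipalities; municipality as a categorical covariate.

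**Stated form.** For city c and period p (0 = pre, 1 = post):

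log(rate) = a + g_c + b·p

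The post/pre rate ratio in city c is exp(a + g_c + b) / exp(a + g_c) = exp(b). The city term cancels, so the ratio is the same in every city. Parameters: 1 intercept + 3 city + 1 period = 5. Municipality does not change over time within a site, so in a within-site comparison it says nothing about how the pre/post change varies between cities.

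**Form needed for an effect by setting.**

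log(rate) = a + g_c + b·p + d_c·p

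The rate ratio in city c is exp(b + d_c). Parameters: 5 + 3 = 8. This gives four city-specific ratios, and the hypothesis that all d_c are zero is a 3-degree-of-freedom heterogeneity test.

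**Illustration.** The city rate ratios and baseline rates below are assumptions, not protocol figures. Each city has 100 sites with 60 months before and 60 after installation. With equal pre and post time, the common ratio from the stated form is total post count / total pre count, which is the mean of the city ratios weighted by baseline rate.

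| Assumed city ratios | Baseline rates per site-month | Common ratio from stated form |
|---|---|---|
| 0.6, 0.8, 1.0, 1.3 | equal (0.01) | 3.7 / 4 = 0.925 |
| 0.6, 0.8, 1.0, 1.3 | 0.02, 0.01, 0.005, 0.005 | 0.0315 / 0.04 = 0.788 |
| 0.5, 0.5, 1.5, 1.5 | equal (0.01) | 4.0 / 4 = 1.00 |

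For the second row: 0.6×0.02 + 0.8×0.01 + 1.0×0.005 + 1.3×0.005 = 0.0315, and the baseline rates sum to 0.04. Fitting both models to the expected counts gave these same common ratios, and the interaction model recovered all four city ratios in each case.

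The first two rows have identical city effects. Only the distribution of collisions between cities differs, yet the common ratio moves from 0.925 to 0.788. The pooled value is an average whose weights depend on where the collisions occur.

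**The case against.** The strongest reply is that the plan already contains city-specific effects. The cross-city paragraph opens by referring back to the within-city analyses, and its claim about different settings can be read as the product of both steps together. This largely stands. Four rate ratios per feature and mode will exist before any pooling. A reader might infer that opposite effects in different cities would be averaged away unseen; the documents do not support that, because a divergent pattern would show in the separate city results. With assumed ratios of 0.6 in two cities and 1.1 in the other two, the pooled value would be 0.85 under equal baseline counts and time (3.4 / 4), or 0.81 under equal information on the log scale (√(0.6×1.1)). In either case the separate models would still target 0.6 and 1.1.

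A second reply is that interaction terms belong in a statistical analysis plan, which is not shown, and that calling municipality one of the covariates does not rule out a product term. This stands in part: the wording shows no decision to leave the term out. But the article does not simply stay silent. It names a model and states what that model will deliver, and the second does not follow from the first. Project 2A shows that effect modification can be named in the same article as a step beyond adjustment.

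A reader might also infer that Objective 1 has the same defect, since it says "Categorical variables will be included in the model representing each of the sites (municipalities) to enable inter-jurisdictional comparisons". It does not. Objective 1 claims only comparisons between jurisdictions. City indicators provide one such comparison, of adjusted active-transportation proportions, and separate models per municipality are planned there too. It makes no claim that effects will be shown to differ by context.

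**Conclusion.** The point holds for the cross-city model of Project 2C and is of moderate weight. As described, that model gives one common post/pre rate ratio per feature and mode and cannot by itself show how the effect varies between cities. What 2C lacks is a formal between-city comparison, not city-specific estimates. The stated 2C objective, estimating the effect of traffic features on collisions, is served by the within-city models and is unaffected.

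The structural result rests on two things: a log-linear pre/post model, which the protocol states, and the literal reading of municipality as a main effect only. It does not depend on the illustrative numbers. The figures 0.925, 0.788 and 1.00 depend wholly on the assumed city ratios and baseline rates and do not predict what this study will find. Power to detect a difference between cities cannot be calculated, because 2C gives no event counts or target effect.

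**What to change.** Amend the section on Inter-municipality comparisons in one of three ways:

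- Add a period (pre/post) × municipality term to the cross-city model, separately for pedestrians and bicyclists, and report the city-specific rate ratios with confidence intervals and a joint heterogeneity test.
- Keep the separate city models and test heterogeneity across their log rate ratios, for example with Cochran's Q on 3 degrees of freedom when all four cities contribute. This needs only the estimates and standard errors already planned.
- If neither is wanted, say that the pooled model estimates an average effect over the cities, and drop the claim that it shows which features work best in which context.

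The change is a sentence or two of text and needs no new data. The first option adds three parameters per feature and mode. With either of the first two, city-specific estimates are less precise than the common one, and the heterogeneity test may have low power where a feature has few sites. A non-significant test should then not be reported as evidence that the effects are equal.

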### Anticipated concerns

It can be difficult to obtain implementation/installation dates for some traffic features [32]. We will focus on traffic features that we are able to obtain sufficient numbers with installation dates. Details of sample size and time pre and post installation will differ for each traffic feature and for each municipality; however, the feasibility of this analysis is supported by our published results from using this approach to estimate the effectiveness of pedestrian countdown signals [52], speed humps [55], school crossing guards [32], cycle lanes [56], and a streetcar right-of-way, in Toronto [57].

#### Project 2D

To estimate the associations between the built environment and child and youth bicyclist-injuries using a case-crossover design

### Study design

We will use a case-crossover design to compare the built environment characteristics of the site where the injury event occurred (injury site) to those at two randomly selected sites (control sites) along the bicyclist’s route before the injury occurred. Our approach uses the design of a study of infrastructure and bicycling injury risk in adults [24]. It overcomes methodological limitations of previous bicycling injury research by controlling for important confounding by personal, weather, and daylight characteristics by using injured bicyclists on a single trip as their own controls, and addressing exposure to injury risk by comparing injury sites to control sites on the route bicycled on the injury trip.

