### Data collection

#### Interview and site selection

We will train a research assistant to conduct the interview using a semi-structured questionnaire to map the route of the injured bicyclist on the injury trip, including any trip continuation after the injury event. Detailed paper maps (including streets and off-street paths) will be used to identify the trip route and injury site. Using a digital map wheel, we will estimate the trip distance and multiply it by two randomly generated proportions to select two control sites along the route. The second of these points will be moved either forward or backward along the route (depending on participants study specific identification number) to match the intersection/non-intersection status of the injury site. We will ask questions on the circumstances of the injury event and characteristics of the injury and control sites on the trip such as street surface conditions, light conditions, presence of construction, and estimated speed. We will also collect data on personal characteristics (age, sex, bicycling experience etc.) and trip characteristics (type of bicycle, clothing colour, weather, time of day) for secondary analyses; the case-crossoverapproach inherently controls for these factors.

We will use the interview procedures and data collection forms that Teschke et al. used with adult bicyclists [24]. Our collaborators with expertise in child and youth injury prevention will modify the interview questions to ensure they were suitable for children and youth. The questionnaire and modifications were pilot tested with additional revisions made prior to initiation of the project.

Given that some children and youth will have mild to severe brain injuries, and that some information may come from very young children, the interviewer will record the source of the interview (child, parent, other proxy respondent, etc.) and rate their confidence in the quality of the interviewee’s description and recall of the bicycling route and site characteristics. We will conduct sensitivity analyses based on the interviewer’s trust in the information quality.

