### Data analysis

Route types will be classified into categories consistent with Teschke et al. [24] We will compare personal characteristics by age group: child (< 13 years old) and youth (13–17 years old) consistent with age categories used in our prior bicycling injury research [14, 59]. We will compare the characteristics of the injury and control sites accounting for the fact that we have matched data (i.e., the same subject contributes the injury and control sites along a given route) [60]. We will use conditional logistic regression analysis to examine the route characteristics related to bicycling injuries. We will add no more independent variables than 10% of the number of discordant pairs (case site location characteristics different than control site location characteristics) [61]. We have used this analytic approach in our previous work [62]. Multiple imputation analysis will be used to assess the influence of missing data on effect estimates [63].

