#### Sample size

Based on our prior work [14, 64, 65] approximately 49% of bicyclists will meet eligibility criteria (injured in an urban location) and will agree to participate. Public Health Agency of Canada injury surveillance data [66] for 2013 indicated there were 1139 child and youth bicycling injuries at the study EDs (Email Communication, [name], Injury Section, Public Health Agency of Canada, June 29, 2016). This number would result in approximately 837 (1139*49% = 558 *1.5 years) eligible injuries from May, 2017-October, 2018. With a sample of 837 injury and matched control sites for each individual, we will be able to detect odds ratios as low as 1.5 with 80% power (0.05 significance level) for a control site exposure prevalence ranging from 10% through 70% [67]. Of note, in the study by Teschke et al. [24], the prevalence of various infrastructure types ranged from 1% (major street with parked cars, shared lane) to 33.5% (downhill grade).

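### Project 2D gives two different sampling frames for control sites, and where controls can only precede the crash the odds ratios for features ordered along a route are biased under no true effect

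*Protocol article*

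**What the plan says.** The Abstract (Methods) and the Project 2D Study design use the same words: the injury site is compared with "two randomly selected sites (control sites) along the bicyclist’s route before the injury occurred".

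The Interview and site selection section, the only place that gives the procedure, reads differently. The interviewer is to "map the route of the injured bicyclist on the injury trip, including any trip continuation after the injury event". Then "we will estimate the trip distance and multiply it by two randomly generated proportions to select two control sites along the route". To match intersection status, "The second of these points will be moved either forward or backward along the route". Nothing there stops a control site from lying beyond the injury site, and nothing says what is done when the trip ended at the crash.

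On the analysis, the Project 2D Data analysis section says: "We will use conditional logistic regression analysis to examine the route characteristics related to bicycling injuries". The Sample size section expects 837 injuries and 80% power for odds ratios as low as 1.5, at control-site exposure prevalences of 10% to 70%.

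**The concern.** Conditional logistic regression treats the three sites in a matched set as exchangeable when a feature has no effect. That fails if controls come only from the part already ridden and the feature has a typical place on a trip, for example local streets near home and larger roads later. Early-route features are then over-represented among controls. Matching within one trip removes confounding by person, weather and daylight. It does not remove route order, because order varies within the set.

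Aligning the summary wording with the procedural text would not be enough. That text maps any continuation, but for a child who did not ride on, the mapped trip still ends at the injury site. All participants were seen in an emergency department, so it cannot be presumed that nearly all continued.

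At stake are the route-type odds ratios, the main product of Project 2D. Under Project 3B they also feed the municipal toolkit. They could mix risk with position on the trip.

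**Working it through.** **The plan's own figures (Project 2D, Sample size).** 1139 × 0.49 × 1.5 = 837.2, so 837 reproduces. With Dupont's matched formula, two controls, odds ratio 1.5, two-sided 5% (sidedness assumed) and a within-set exposure correlation of 0.2 (assumed), power is 81.9% at 10% prevalence and 97.4% at 70%. The power statement also holds. Neither figure is affected by this point.

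**Assumptions for the bias check.** No true effect. The injury point T is uniform on the planned route, scaled to length 1 (constant risk per metre). Controls are uniform on (0, T) if the mapped trip ends at the crash and on (0, 1) if the child continued. The feature's place on the route and the share continuing are not in the documents, so both are varied. Matching of the second control on intersection status is not modelled.

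**Closed form, one control, nobody continuing, feature on (a, b):**

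- P(case exposed, control not) = ∫ from a to b of (a/t) dt = a·ln(b/a)
- P(control exposed, case not) = ∫ from b to 1 of ((b − a)/t) dt = (b − a)·ln(1/b)
- Null odds ratio = a·ln(b/a) / [(b − a)·ln(1/b)]

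Feature on 20–80% of the route: 0.2·ln 4 = 0.277; 0.6·ln 1.25 = 0.134; ratio 2.07. Feature on the middle third: 1.71. For a short feature at position x the ratio tends to 1/ln(1/x), which equals 1 at x = 1/e, about 37% of the route. Short features beyond that point look hazardous and earlier ones look protective.

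**Two controls, conditional logistic regression.** Odds ratios are from 1,000,000 simulated sets. Rejection rates at the 5% level are from 1,000 studies of 837 sets.

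| Feature's place on planned route | OR, none continue | OR, half continue | OR, all continue | Rejected, none / half |
|---|---|---|---|---|
| 20–80% | 2.19 | 1.40 | 1.00 | 100% / 95% |
| 33–67% | 1.75 | 1.28 | 1.00 | 100% / 73% |
| 40–60% | 1.61 | 1.23 | 1.00 | 98% / 46% |
| 10–25%, 40–55%, 70–85% | 1.15 | 1.07 | 1.00 | 38% / 13% |
| 25–50% | 1.00 | 1.00 | 1.00 | 6% / 6% |
| 20–50% | 0.87 | 0.94 | 1.00 | 25% / 9% |
| 10–30%, 50–70% | 0.86 | 0.93 | 1.00 | 39% / 14% |
| 10–60% | 0.69 | 0.84 | 1.00 | 97% / 45% |

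The all-continue column is also the result of drawing controls over the whole intended trip for every child; rejection there was about 4% to 6%. For the middle-third feature the odds ratio falls steadily as more riders continue: 1.75, 1.48, 1.28, 1.12 and 1.00 at 0, 25, 50, 75 and 100%. A feature placed at random along each route gives 1.00 even if nobody continues.

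The table gives examples and not bounds. By the one-control formula, a feature on 60–80% gives 3.87 and one on 10–20% gives 0.43.

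**The case against.** The strongest reply is that the summary lines are shorthand. The procedural text maps the continuation and draws over the trip distance, and the Study design section itself closes by describing control sites as lying on the route ridden on the injury trip. This stands in part. A reader might infer that controls are always taken from before the crash and that the injury site is always last. The documents do not support that for children who rode on.

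Second, the layouts are invented. This also stands. A reader might infer that mid-route features will look hazardous as a rule. The table shows odds ratios above 1, at 1 and below 1, depending on layout. Nor are all the false odds ratios at or above 1.5: in the table only three are, all with nobody continuing.

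Third, a reader might infer that position can never be adjusted for. It separates cases from controls completely only in sets whose controls all precede the injury. Sets from continuing riders can have controls on either side.

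Fourth, the design and forms follow an adult study that is not shown, and its forms may deal with trips ended by the crash. That is possible, but it does not reconcile the two frames stated in this article.

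Finally, drawing controls from stretches never ridden departs from the stated rationale of comparing sites on the route cycled, and relies on recall that the protocol already treats with caution. This is a real cost and is the reason for the sensitivity analysis below.

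**Conclusion.** The point holds as a conflict with consequences. The article states two sampling frames. One produces position bias for every child, the other for those whose mapped trip ended at the crash, wherever features are ordered along routes. For the layouts tabulated, the null odds ratio runs from about 0.7 to 2.2 with nobody continuing and from about 0.84 to 1.4 with half continuing. The upper part of the first range exceeds the target of 1.5. It is 1.00 when controls are drawn over the whole intended trip, or when features have no order.

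These sizes rest on constant risk per metre, assumed layouts and an assumed share continuing. The documents do not show that any particular Project 2D estimate will be biased, by how much, or in which direction. They do leave open a frame under which it can be, and that can be settled at site selection.

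**What to change.** State one frame in the Abstract, the Study design and the Interview and site selection sections: both random proportions are drawn over the whole trip from origin to destination, and not only over the part before the injury.

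Where the crash ended the trip, ask for the intended destination, map the route to it and draw over that distance. At points not reached, use only items from the blinded site observation, since recalled items such as surface condition, light and estimated speed do not exist there.

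Report a sensitivity analysis limited to trips that were continued or completed. This also serves children already interviewed without the extra question.

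The cost is one interview question, one selection rule and aligned wording. The downside is that the unridden part rests on stated intention and has no recalled transient items. The restricted analysis is smaller and may favour milder injuries, so it should be read beside the main result and not in place of it.
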